### Children

#### Experience of Violence

At pre-assessment and at the follow-up assessments, children's exposure to violence by teachers in the past week will be assessed using an adapted version of the Conflict Tactic Scale (CTS) including 16 items on experienced physical violence, 7 items on experienced emotional violence and 3 items on witnessed violence by teachers. These items are scored on a 6-point Likert scale ranging from 0 (never) to 5 (more than 10 times). Subscale scores are derived by summing up all item scores. The original CTS has been used worldwide as a measure of physical and emotional maltreatment of children and its validity has been demonstrated by numerous studies (23). The CTS has also been used to assess students' self-reported experiences of violence by teachers in different cultural settings, e.g., in Tanzania (8) and Turkey (24). While the total score of physical and emotional violence had acceptable (α = 0.72) to excellent Cronbach's alpha coefficient (α = 0.88) in a previous study (24, 25), the two subscales of physical violence and emotional violence exhibited lower internal consistency (α = 0.55 and α = 0.60, respectively) in another study (8). The low reliability can be explained by the fact that the items measure rather rare events and that the correlation between items, which is the basis of alpha, is low due to extreme skewness (26).

#### Mental Health Problems

The Pediatric Symptom Checklist—Youth Report [PSC-Y; (27)] will be used to assess children‘s emotional and behavioral problems. The PSC-Y consists of 35 items rated on a 3-point Likert scale from 0 (never) to 2 (often), which can be summed up to a total score of emotional and behavioral problems ranging from 0 to 70. Factor-analyses of the parent- and youth-report version of the PSC revealed a 3-factor structure of internalizing problems, externalizing problems and attention problems (28, 29). In the original validation study, the PSC-Y demonstrated good concurrent validity with parent- and teacher-reports of children's emotional and behavioral problems as well as moderate test-retest-reliability (27). Adapted versions of the PSC haven been used in different cultural settings including Botswana (30), Uganda (31) and Turkey (32) with good psychometric properties, indicating the instrument‘s cross-cultural applicability. For instance, in a sample of children and adolescents in Botswana, the PSC-Y showed high internal consistency with a Cronbach's alpha of 0.89 and also good sensitivity and specificity to detect children with increased levels of mental health problems (30).

#### Quality of Life

The KIDSCREEN-10 (33) will be used to assess children‘s perceived quality of life. The KIDSCREEN-10 conceptualizes quality of life as a multidimensional construct covering physical, emotional, social and behavioral aspects of well-being and functioning. The 10 items referring to the past week are rated on a 5-point Likert scale from 0 (not at all) to 5 (extremely). The KIDSCREEN-10 has shown to be a valid (Cronbach's alpha of 0.82 and test-retest reliability of 0.70) and cross-cultural comparable tool to assess children's and adolescents' self-reported quality of life (33).

#### Cognitive Functioning

Four classical tasks implemented in the Android application Psych Lab 101 (34) will be used to assess different aspects of children's cognitive functioning: A visual search task (selective attention), a numerical stroop task (ability to resist interference by distracting information), a delayed match-to-sample task (working memory capacity) and a continuous performance task (impulsivity). These tasks were selected because they are independent of language and they cover “core” cognitive abilities that have been shown affected by exposure to maltreatment (35, 36). Prior to data collection, a pilot-assessment will be conducted to ensure feasibility of the tablet-based assessment.

#### Academic Performance

Children's academic performance will be measured using a standardized numeracy and literacy test. This test is based on standardized tests of numeracy and literacy skills developed by the Uwezo initiative (37), which have been applied in large-scale surveys in East Africa to assess learning outcomes of primary school children. The included tasks will focus on essential numeracy and literacy skills independent of national curriculum and will be evaluated by educational experts in terms of their applicability for the study context. In addition, we will request from the school administration children's scores in Mathematics, Haitian Creole, English, Science, Social Science, and General Studies in the mid-term exam as a direct indicator of school performance.

#### Social Competence

Children's social competence will be assessed in two ways. First, a well-established peer-nomination procedure, the social cognitive map (SCM) technique (38), will be applied to assess children‘s social status in their peer networks. This procedure asks children to name a group of children in their class to which they belong as well as other groups of friends in their class. Based on the number of nominations as members of a group, the social centrality status of individual children can be determined (39). Moreover, children are asked to nominate three classmates they like most and three they like least, which yields an indicator of social preference status for each child. The SCM technique makes it possible to reliably identify social groups with proportions of respondents from a social network as small as 50% (39). The technique has been successfully implemented in a previous study with primary school children in different cultural settings e.g., in Tanzania (40). Second, the 8-item short form of the PROMIS pediatric peer relationship scale (41) will be used to assess the quality of children‘s relationships with peers and friends through their self-report. The items are rated on a 5-point Likert scale from 0 (never) to 5 (almost always) and refer to the past 7 days. The scale has been used in various cultural settings including a sample of child patients in Malawi (42). Cronbach's alpha coefficients ranged between 0.71 (42) and 0.85 (43), indicating acceptable to good internal consistency.

#### Peer Violence

We will assess children's experiences of violence by peers using the 24-item version of the Multidimensional Peer Victimization Scale (MPVS) (44). Four items each assesses the six subtypes physical victimization, verbal victimization, social manipulation, attacks on property, electronic victimization and social rebuff. The original 16-item and the 24-item version of the MPVS have shown good psychometric quality with Cronbach's alpha coefficients ranging from 0.74 to 0.96 (44). We will additionally assess sexual victimization by peers using four items from the adolescent version of the Sexual Experiences Survey (45). Two items each will cover sexual harassment and sexual assault by peers.

### Teachers

#### Use of Violent Discipline

Teachers' use of physical and emotional violence against students in the past week will be assessed using the same modified version of the CTS as for children. Hence, the items (except for the three items on witnessed violence) and the answer scale are the same (see above). The CTS scale has proved useful in assessing teachers' self-reported use of violence in the classroom across various cultural settings (24, 25, 46). Cronbach alpha coefficients ranged between 0.73 (46) and 0.83 (24), indicating acceptable to good internal consistency.

#### Attitudes Toward Discipline

We will use an adaptation of the CTS to assess teacher's positive attitude toward the use of violent discipline (Nkuba et al., 2018). The items are the same as described before, but this time scored on a four-point scale Likert scale ranging from 0 (never OK) to 3 (always or almost always OK). The scores for each subscale are then summed up into one score for physical violence (ranging from 0 to 48) and one for emotional violence (ranging from 0 to 21). The measure showed good internal consistency (Cronbach's alpha of 0.84) in a previous study with teachers in Tanzania (46).

### Measures Against Bias

To minimize recruitment bias, a stratified random sampling approach is used. To minimize bias from using unvalidated outcome measures, a careful selection of the assessment instruments has been undertaken. Since the school allocation will be executed at the cluster level and by independent researchers, the data collectors will be blind to the treatment conditions of the schools. To further minimize the risk of contamination between treatment conditions, there will be no contact between the intervention facilitators and data collectors. Although the intervention participants will not be blind regarding whether they belong to the treatment or the control group, the use of violence by teachers will also be assessed through children's self-reported exposure to violence. To avoid incomplete accounting of participants and outcome events, the analysis will treat groups as randomized (“intention to treat”).

### Statistical Analysis

Pre-assessment data will be used to assess the prevalence of maltreatment and violence as well as children's mental health and well-being. A longitudinal analysis (including the follow-up assessments) will then be undertaken using an intent-to-treat approach. As drop-outs and missing data at follow-up assessment are likely given the longitudinal study design, we aim to apply full information maximum likelihood estimation to obtain unbiased parameter estimates.

Our main analysis of the primary and secondary outcomes will be time × group interaction effects using multilevel linear modeling. By randomly assigning schools to the intervention and control condition, we do not expect systematic differences between schools, teachers, and students in the two groups. However, we will examine differences between the groups in sociodemographic characteristics on the level of the school (e.g., material conditions), teachers (e.g., socioeconomic status, teaching experience) and students (e.g., socioeconomic status, gender). In case of significant differences, we will control for these differences in all analyses. Latent growth modeling or cross-lagged path models will be used to estimate the directional influence of violence by teachers on primary and secondary outcome variables over time. Results will be presented including appropriate effects sizes and with a measure of precision (95% confidence intervals). Effect sizes of η^2^ ≥ 0.01, η^2^ ≥ 0.06 and η^2^ ≥ 0.14 will be considered as small, moderate, and large effects, respectively (47).

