### Power Calculation

We conducted an *a priori* power analyses to determine the number of clusters (schools) for the trial as well as the number of participants (students and teachers) per cluster. Following a previous trial of ICC-T at Tanzanian secondary schools (21), we expected moderate (δ = 0.25) and large effects (δ = 0.35) on student-reported and teacher-reported violence by teachers, respectively. Based on previous and ongoing trials of ICC-T (3, 20, 21), we expected an intra-class correlation coefficient (ICC) of 0.03 and 0.05 for student- and teacher-reported violence, respectively. Moreover, the covariance between baseline and follow-up scores of violence at the school level was *r* = 0.30. Given all specified parameters (α = 0.05; power = 0.80; effect size students: δ = 0.25, effect size teachers: δ = 0.35; ICC students = 0.03, ICC teacher = 0.03; *R* = 0.30), no drop out at the school-level and an estimated dropout rate of 30% for teachers and 25% for students, in total 36 schools with 28 students and 13 teachers per school are required to detect the expected effects. The total sample size is therefore at least *n* = 1,008 children and *n* = 468 teachers.

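### Full maximum likelihood for the time × group test on 36 randomised schools gives a type I error slightly above 5%; REML with small-sample degrees of freedom would correct this without losing the missing-data property

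*Protocol article*

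**What the plan says.** The Statistical Analysis section of the protocol article states: "Our main analysis of the primary and secondary outcomes will be time × group interaction effects using multilevel linear modeling". In the paragraph before, drop-out and missing follow-up data are given as the reason for the estimator: "we aim to apply full information maximum likelihood estimation to obtain unbiased parameter estimates". The section names no random effects, reference distribution or degrees-of-freedom method. It also plans latent growth or cross-lagged path models.

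The Power Calculation section concludes that "36 schools with 28 students and 13 teachers per school are required to detect the expected effects", with "α = 0.05; power = 0.80; effect size students: δ = 0.25, effect size teachers: δ = 0.35" and "an estimated dropout rate of 30% for teachers and 25% for students". It expects an intra-class correlation ("ICC) of 0.03 and 0.05 for student- and teacher-reported violence, respectively"), but its parameter list has "ICC students = 0.03, ICC teacher = 0.03". It also says that "the covariance between baseline and follow-up scores of violence at the school level was" r = 0.30, and the parameter list then writes the same value as R = 0.30.

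Under Schools, allocation is three versus three schools or school clusters in each of six communes.

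**The concern.** The treatment effect is a contrast between 36 randomised units, so its precision depends on variance estimated from about 34 degrees of freedom. Full maximum likelihood does not adjust variance components for the fixed effects it has fitted, and its default Wald test uses a normal reference. Both push the type I error on the primary comparison upwards.

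There is also a conditional issue. A school intercept that is constant over time cancels out of a time × group contrast. What remains at school level is the part of school variance that changes between waves. The power calculation implies that this part is not zero, because the school-level association over time is well below 1. If the fitted model had no term for it, the test would treat people in the same school as independent in their change scores.

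**Working it through.** **Inputs.** From the Power Calculation section: J = 36 schools; 28 students and 13 teachers per school, so m = 28 × 0.75 = 21 students and 13 × 0.70 = 9.1 teachers after drop-out; intra-class correlation (ρ) 0.03 for students and 0.05 (text) or 0.03 (parameter list) for teachers; school-level association 0.30. Assumed: two-sided α, balanced data, two time points, within-person correlation r_i = 0.3 to 0.7 (not given in the article).

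**1. The plan's own figure.** Var = 4[ρ(1 − R²) + (1 − ρ)/m]/J, with 0.30 read as a school-level R².
- Students: 4[0.03 × 0.70 + 0.97/21]/36 = 0.00747, SE 0.0864, and 0.25/0.0864 = 2.89. Power is 80.3% with t on 34 df (82.5% with a normal reference).
- Teachers, ρ = 0.03: SE 0.1191, 0.35/0.1191 = 2.94, power 81.5% with t. With ρ = 0.05, power is 78.0% (t) or 80.3% (normal).

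So 36 schools is reproduced when 0.30 is an R². Read as a correlation (R² = 0.09), students would need 40 schools (t) or 38 (normal).

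**2. Maximum likelihood with correct random effects.** In balanced data the contrast is a comparison of 36 school-mean changes between two arms. ML divides the sum of squares by 36, and REML divides it by 34.
- SE ratio = √(34/36) = 0.972, that is, about 3% too small.
- Size with a normal reference = P(|t₃₄| > 1.96 × 0.972) = 6.5%.
- Simulation (20,000 runs per setting, students and teachers, both readings of 0.30): ML with a normal reference 5.9-6.5%; REML with t on 34 df 4.5-5.0%. Separate simulations of the same contrast gave 5.5-6.6% and 4.3-5.1%.

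**3. If school and person intercepts are fitted with no school-by-wave term.** Let r_s be the school-level correlation between waves. Up to a common factor:
- true variance T = ρ(1 − r_s) + (1 − ρ)(1 − r_i)/m
- model variance M = [ρ(1 − r_s) + (1 − ρ)(1 − r_i)]/m
- SE ratio = √(M/T); size ≈ 2[1 − Φ(1.96√(M/T))]

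Worked case, students, r_s = 0.30, r_i = 0.3: T = 0.021 + 0.679/21 = 0.0533; M = 0.700/21 = 0.0333; SE ratio 0.79; size 12.1%.

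If 0.30 is an R², r_s = √0.30 = 0.55 and about 45% of school variance is wave-specific. If it is a correlation, about 70% is.

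| | r_s = 0.55, r_i = 0.3 / 0.5 / 0.7 | r_s = 0.30, r_i = 0.3 / 0.5 / 0.7 |
|---|---|---|
| Students, ρ = 0.03 | 9.7 / 11.5 / 15.4% | 12.1 / 14.7 / 20.1% |
| Teachers, ρ = 0.05 | 8.2 / 9.4 / 12.1% | 9.8 / 11.6 / 15.4% |

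Simulation of the end cases agreed: students 9.7-15.3% and 12.3-20.2%, teachers 8.1-11.8% and 10.2-15.8%. Referring the same SE ratios to t on 34 df instead of the normal gives the rounded upper ends of 21% and 16% for r_s = 0.30. With teacher ρ = 0.03, the formula gives 6.9-9.3% (r_s = 0.55) and 7.9-11.5% (r_s = 0.30).

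**4. If only a school intercept is fitted, with no person intercept.** With r_s = 0.30 and r_i = 0, 0.3, 0.5 and 0.7, the SE ratio is 0.84, 0.94, 1.03 and 1.16 for students, and 0.88, 1.00, 1.11 and 1.28 for teachers (ρ = 0.05). The error can go either way.

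**The case against.** The strongest answer is that the article does not state a faulty model. It names a multilevel time × group analysis and leaves the random effects and the reference distribution open. A journal article commonly leaves these to the analysis plan, which is not at hand, so their absence is no fault. The FIML sentence is about missing data and is worded as an aim. A t reference can be used with ML estimates, and FIML is standard for the latent growth and cross-lagged models in the same section. With correct random effects the excess is only one to one and a half percentage points. All of this stands, and it is why the severity is low and the larger figures are conditional.

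Three stronger readings are tempting, and the article supports none of them.
- A reader might infer that standard errors will be too small because only school intercepts are fitted. The article does not say so, and step 4 shows that the direction under that model depends on a within-person correlation it does not give.
- A reader might take 70% of school variance as wave-specific by the plan's own figure. The 0.30 is ambiguous, and the planned 36 schools is reproduced with it as an R², which gives about 45%.
- A reader might add the six communes and quote a type I error of 7.7-9.1%. Those values come from a single-wave comparison with commune terms, and the highest uses an intra-class correlation of 0.10, which is not in the article. The Statistical Analysis section does not put commune in the model, and a commune main effect would drop out of a time × group contrast.

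What the objection does not remove is that full maximum likelihood is the estimator the article names, and that its missing-data reason does not require it for this model.

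**Conclusion.** The point holds in a limited form. For the stated estimator on 36 randomised units, the standard error is about 3% too small and the type I error is about 6 to 6.6% with the usual normal reference, even when the random effects are right. This rests on balanced data and two arms, and needs no assumed misspecification.

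The further inflation is conditional on a model with school and person intercepts and no school-by-wave term: about 10-15% for students and 8-12% for teachers if 0.30 is an R-squared, or about 12-21% and 10-16% if it is a correlation. Those ranges assume a within-person correlation of 0.3-0.7, two time points and a teacher intra-class correlation of 0.05. They show what the model must carry. They do not show that the planned analysis leaves it out. Low severity.

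**What to change.** For the main analysis, state that the arm-by-wave model is fitted by REML to all available waves. Include random effects for the randomised unit (school or school cluster), unit-by-wave and person, and use Kenward-Roger or Satterthwaite degrees of freedom. REML uses the same available outcome data under the same missing-at-random assumption, so the reason given for FIML is still met. FIML can stay for the latent growth and cross-lagged models. It would also help to say whether 0.30 is a correlation or an R-squared.

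The cost is wording and slightly wider intervals. REML does not handle missing covariates as FIML can, so covariates with gaps would need their own rule. The change does not itself call for more schools: on the parameter list's values with 0.30 as an R-squared, 36 schools give 80.3% power (students) and 81.5% (teachers) with t on 34 df.

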### Schools

Selected schools must meet the following inclusion criteria: (1) teachers should not have received any training on violence prevention in the past; (2) the school should be a community or public mixed-gender school; (3) the school should have at least 13 teachers and at least 40 children in the 4th class of primary school (see power calculation above). In case of fewer than 13 teachers or fewer than 40 students in the relevant grade, the selected school will be combined with a neighboring school (within 15 km) into a school cluster. Schools that meet these criteria will be listed in alphabetical order and a random selection of six schools/school clusters in each of the six communes of Haiti's Département du Nord will be executed using http://www.random.org. In each commune, three schools or school clusters will be allocated to the treatment group (i.e., teachers will receive the ICC-T sessions), and the other three schools or school clusters into the control group (i.e., teachers will not receive the ICC-T sessions) after baseline assessment. All random selections and allocations will be performed by independent research staff.

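### The main test is a time × group interaction with no baseline adjustment stated, yet 36 schools fits a baseline-adjusted analysis; power below 80% is likely but depends on a correlation the plan does not give

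*Protocol article*

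**What the plan says.** The Statistical Analysis section fixes the main test: "Our main analysis of the primary and secondary outcomes will be time × group interaction effects using multilevel linear modeling". The covariates it plans are sociodemographic characteristics that turn out to differ significantly between arms. The baseline value of the outcome is not among them, and nothing says that arm means are held equal at baseline. Missing data are to be handled by full information maximum likelihood.

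The Power Calculation section credits a baseline association: "the covariance between baseline and follow-up scores of violence at the school level was *r* = 0.30". The same quantity reappears in the parameter list as a capital R. No individual-level correlation is given. The narrative says "we expected an intra-class correlation coefficient (ICC) of 0.03 and 0.05 for student- and teacher-reported violence, respectively", while the parameter list says "ICC students = 0.03, ICC teacher = 0.03", so there are two teacher ICCs. The effects are stated as "we expected moderate (δ = 0.25) and large effects (δ = 0.35) on student-reported and teacher-reported violence by teachers, respectively". The result is 36 schools with 28 students and 13 teachers each, for 80% power at α = 0.05.

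The Schools section places allocation after the baseline survey: three of six schools in each commune go to treatment and the other three "into the control group (i.e., teachers will not receive the ICC-T sessions) after baseline assessment".

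**The concern.** With a free arm difference at baseline, a time × group interaction compares change scores. Its variance is proportional to 2(1 − r), where r is the baseline to follow-up correlation. Adjusting for baseline gives 1 − r². Ignoring baseline gives 1. At r = 0.30 these are 1.40, 0.91 and 1.00, so the change comparison is noisier than discarding the baseline survey altogether.

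The sample size treats the baseline association as a gain in precision, which fits an adjusted analysis. If the named test is fitted in its usual form, the stated 80% belongs to a different analysis. A 36-school trial could then miss an effect it was sized to detect, although the data needed to avoid this will already have been collected.

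**Working it through.** **Inputs from the Power Calculation section.** α = 0.05 (two-sided assumed); δ = 0.25 (students) and 0.35 (teachers); ICC 0.03 (students) and 0.03 or 0.05 (teachers); 18 schools per arm. After dropout, m = 28 × 0.75 = 21 students and 13 × 0.70 = 9.1 teachers per school. School-level association: 0.30.

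**Assumptions.** Total SD 1 at each wave; individual-level correlation rᵢ of 0.3 to 0.6; one follow-up.

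**Formulas.** B = ICC and W = (1 − ICC)/m. SE = √(2V/18). Power comes from a noncentral t with 34 df, or 33 df with a covariate.

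- Follow-up only: V = B + W
- Difference in change: V = 2B(1 − rₛ) + 2W(1 − rᵢ)
- Baseline-adjusted: V = B(1 − rₛ²) + W(1 − rᵢ²)

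W is 0.97/21 = 0.0462 (students), 0.97/9.1 = 0.1066 (teachers, ICC 0.03) and 0.95/9.1 = 0.1044 (teachers, ICC 0.05). In each case W exceeds B, so the individual-level correlation that the plan omits matters more than the school-level one it gives.

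**Reproducing 36 schools.** Read 0.30 as the share of school-level variance explained by baseline (R²), with teacher ICC 0.03, so V = 0.7B + W. For students V = 0.021 + 0.0462 = 0.0672 and power is 80.2%. For teachers V = 0.021 + 0.1066 = 0.1276 and power is 81.4%. On the t-test both outcomes need exactly 36 schools.

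The alternative is to read 0.30 as a correlation at both levels. The normal approximation for the total number of schools is 4V(1.96 + 0.842)²/δ²:

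| Analysis | Students | Teachers, ICC 0.03 | Teachers, ICC 0.05 |
|---|---|---|---|
| Baseline-adjusted | 34.8 | 31.9 | 36.0 |
| Follow-up only | 38.3 | 35.0 | 39.6 |
| Difference in change | 53.6 | 49.0 | 55.4 |

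For example, for change in students V = 1.4 × 0.0762 = 0.1067, and 4 × 0.1067 × 7.85/0.0625 = 53.6. Either adjusted reading is compatible with 36 schools. A change analysis at r = 0.30 is not.

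**Power with 36 schools, single follow-up (%), change / adjusted.** A school correlation of 0.55 is √0.30, the R² reading.

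| School r, individual r | Students | Teachers, ICC 0.03 | Teachers, ICC 0.05 |
|---|---|---|---|
| 0.30, 0.30 | 60.7 / 78.9 | 64.5 / 82.4 | 59.3 / 77.6 |
| 0.30, 0.60 | 73.7 / 86.3 | 81.6 / 90.9 | 74.0 / 86.0 |
| 0.55, 0.30 | 67.2 / 82.6 | 68.1 / 84.3 | 64.5 / 80.7 |
| 0.55, 0.60 | 82.1 / 89.9 | 86.0 / 92.7 | 81.1 / 89.1 |

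Follow-up only gives 75.2%, 78.8% and 73.8%. Adjustment is ahead in every cell, by 6.7 points (92.7 − 86.0) to 18.3 points (77.6 − 59.3). The direction does not depend on the inputs: 2(1 − r) − (1 − r²) = (1 − r)², which is positive for any r below 1.

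**Two further checks.** Full information maximum likelihood, with dropouts contributing baseline only and school r = 0.30, adds about 1 to 4 points to the unconstrained change test (students at rᵢ = 0.3: 60.7% to 63.0%). Averaging the two follow-ups, with 0.30 between every pair of waves, gives a variance factor of 0.65 + 1 − 0.60 = 1.05 for change and 0.65 − 0.09 = 0.56 adjusted. Power is then 72–77% against 93–96%.

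**The case against.** The strongest reply is that a free baseline difference is inferred. A model with a common baseline mean is also tested through arm-by-wave terms, so it could sit under the existing sentence, and exact parameterisation is often left to an analysis plan. This stands in part: the text does not exclude such a model. It does not state one either, and the conventional fit of time, group and their interaction leaves the baseline difference free.

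The second reply is that 0.30 is a school-level figure and its meaning is unclear. This stands. A reader might infer that the plan's own correlation puts the test at 60–74% power, or that it certainly misses 80%. The documents do not support either statement. The upper end of that range needs an assumed individual-level correlation of 0.6. Under the listed teacher ICC of 0.03, or the R² reading, change power passes 80% at that correlation.

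Third, the interaction is a valid test in a randomised trial, with no bias and no inflated type I error. This also stands and limits the severity.

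A reader might also fear that time enters as a straight line, which would force the 18-month effect to be three times the 6-month effect. The main-analysis sentence does not say so, and growth modelling is named for a different question. That worry is not part of this point.

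**Conclusion.** The point holds as a mismatch between the named main test and the basis of the sample size, and as an avoidable loss of precision. With 0.30 at both levels, a single follow-up and a free baseline difference, power is about 61% (students) and 59–65% (teachers), below even a follow-up-only comparison (75% and 74–79%). With an assumed individual-level correlation of 0.6 it is 74% and 74–82%. If 0.30 is an R², it is 65–68% at an individual correlation of 0.3 and 81–86% at 0.6.

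A shortfall below 80% is therefore likely, not certain. High individual-level correlations are not obvious for the student measure: the Experience of Violence section describes past-week recall of rare, extremely skewed events, with subscale alphas of 0.55 and 0.60 in one study (total-score alphas were 0.72 to 0.88). The advantage of baseline adjustment, about 7 to 18 points in the single-follow-up scenarios shown, does not depend on which reading is right. This should be fixed, but it does not threaten the validity of the trial.

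**What to change.** Replace the main-analysis sentence with one of two statements. Either the main analysis is a constrained longitudinal model with a common baseline mean in both arms and arm-by-wave contrasts at 6 and 18 months, or it is follow-up regressed on arm with the baseline score as covariate. Both are multilevel. Allocation after baseline justifies the common mean by design.

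Then restate power for that model. Give the school-level and individual-level correlations separately, say whether 0.30 is a correlation or an R², and use a single teacher ICC.

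The cost is one sentence of analysis wording and a revised power paragraph. No new data are needed. The constrained model still uses every participant with any wave under full information maximum likelihood.
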